#### Home exercise protocol

The treatment protocol of the study emphasises home exercise because in a previous study of the mechanism of yoga on the treatment of CLBP, the biggest mediator on decreased disability was increased self-efficacy [84]. The participants in both groups will be instructed to practice the prescribed exercises as many days as possible in a week. The maximum recommended daily time for exercise will be 20 min per day. Participants will be instructed to continue any other exercises they performed before the start of the study.

The general home instructions provided on the sheets are as follows:Maintain a neutral lumbar spine during the exercises.Synchronise your breathing with the movements (Note: The breathing instructions are only included on the exercise sheets for group 2).Have breaks between sets and exercises according to your individual needs.Try to practice your exercises regularly/once a day.Remember to regularly update your home diary.

The home exercise sheets are accompanied by individually prescribed repetitions and sets of each exercise from the first author. The participants will have been given the possibility of contacting the first author via email or phone for further clarification of any exercise-related matter. All exercises used in the study with original written home instructions translated from Finnish with breathing instructions are included ins Appendices 1, 2 and 3. The breathing instructions comprise the only difference between the home exercise sheets; they are only provided to group 2.

The protocol of the study attempts to promote identical clinical encounters and treatments for both groups with only the difference of the SBTs add-on for group 2. Different aspects of these efforts are summarised in Table 3.

**Table 3 Tab3:** Summary of efforts to promote practically identical clinical practice exercise programmes

Clinical entity	Aim
Inclusion and exclusion criteria	Include only subjects who are adults with low back pain lasting more than three months (pain sensation more than three days per week) to promote a uniform pain population
	Exclude known cardiovascular, respiratory, rheumatic and neurological diseases potentially affecting breathing mechanics and hence potentially affecting the effects of SBTs
Clinical assessment before inclusion	Include only participants with movement control impairment with exactly similar test batteries to promote homogeneity of treatment and physical performance heterogeneity between the groups
	Include only participants with non-specific CLBP, excluding participants with symptomatic nerve root pathology due to intervertebral disc herniation or lumbar spinal stenosis
Single-clinician study design	The aim is to minimize the intervention differences and effects of contextual factors of clinic settings, such as environment, interior design and therapists’ behaviour, communication and approach to treatment
Exercise	The research appointment follows a similar frequency over eight weeks with the aim of uniform treatment between groups
	There will be a similar number of exercises delivered to the subject in each clinical visit to promote uniform treatment between groups
	Clinical instructions for both groups concentrate on the treatment of movement control impairment
	The exact exercises are chosen according to individual movement impairment, but similar exercises are emphasized for all participants
	Identical general instructions for both groups
Other interventions	The aim is to exclude other evidence-based interventions in order to evaluate more precisely the outcome differences of the study groups

#### Data analysis

Descriptive statistical methods will be used. Statistical analysis will be performed using SPSS version 25 (IBM SPSS Statistics for Windows, Version 25.0. Armonk, NY: IBM Corp.). The normality of the data will be checked by Shapiro-Wilks tests. Demographics data will be shown as percentages or means with standard deviations or medians, with ranges depending on the distribution of the variables. The results of the PROMs will be presented as means (Standard deviation or 95% confidence interval, lower and upper bounds) as recommended on CONSORT 2010 statement: extension to randomised pilot and feasibility trials [85] Furthermore, we will follow the general recommendation of feasibility study sample size of 30 subjects [51].

The external data analyst, who is not involved in planning or conducting the study, will independently collect data from electronic data storage and carry out the data analysis of the comparison between groups. Moreover, the data analyst is blinded to the aims of the study and group intervention differences to increase the objectivity of the group comparison.

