### Objectives

To assess the feasibility of a clinical study protocol, including an SBTs protocol, eligibility criteria, randomization and dropout rates.To quantify the changes in PROMs to help determine whether progression to a full-scale trial is worthwhile and to inform the choice of the most relevant and responsive PROM for a larger-scale study.To quantify self-adherence levels to home exercise and to monitor possible pain medication and other treatment modality usage, as well as possible adverse events and injuries during exercise using a home diary.

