### Participants

#### Eligibility criteria

The participants will be eligible for the study if they meet all inclusion and no exclusion criteria.

Inclusion Criteria:Males and females aged 18–68 yearsLow back pain lasting more than 3 months (pain sensation more than 3 days per week)A numerical pain scale of 4 or higher on a scale of 0 to 10 to prevent floor effects in outcome measurement [47]Roland-Morris Disability Questionnaire score of 5 or higher on a scale of 0 to 24 to prevent floor effects in outcome measurement [48]Physically able to perform movement control tests and provide written informed consent ≥ 2/6 positive low back movement control tests as described by Luomajoki et al., which are well-documented and valid tests of movement control dysfunction on participants with CLBP [12, 13, 49]. The tests are:Waiters bow test for assessment of flexion movement control impairmentDorsal tilt of pelvis for assessment of extension movement control impairmentOne leg stance for assessment of lateral flexion and/or rotational movement control impairmentSitting knee extension for assessment of flexion or rotational movement control impairmentRocking backwards for assessment of flexion movement control impairment and rocking forwards for assessment of extension movement control impairmentProne lying active knee flexion assessment of extension and/or rotational movement control impairment

Exclusion Criteria:Any history of malignancyNeurological disease affecting the central nervous system (MS, dementia)Rheumatic disease (fibromyalgia, ankylosing spondylitis/rheumatoid arthritis)Chronic obstructive pulmonary disease or other diseases that affect the lungs and cause breathing problemsSpinal surgery in the last 12 monthsA cardiac pacemakerPregnancy during the data collectionSigns and symptoms of lumbar nerve root pathology during the eligibility assessment following neurological examination.aToe and heel walk three metresbLower extremity reflexescSitting Slump testsdFemoral nerve stretches tests on side lyingeSupine active and passive straight leg raises on ipsi- and contralateral legs

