#### Recruitment

The research advertisement for the clinical trial will be presented on the first author’s private clinic webpage. In addition, different national Finnish musculoskeletal pain and spine-related organisations, chronic pain peer support groups, and healthcare colleagues will promote the study on their web pages and social media.

Potentially eligible patients meeting the criteria for this study will be invited to read the participant information sheet and consider enrolling in the study. Enrolled participants will book eligibility assessment appointments at the first author’s clinic, where written consent for the study will be given. After written consent, neurological examination of nerve root pathology and low back movement control clinical tests as described by Luomajoki et al. [12, 13] will be carried out as described in detail above.

After the eligibility assessment, the study participants will complete study questionnaires on the webpages of Navisec Health at home. Navisec Health is a Finnish company providing an electronic platform with strong electronic authentication for data collection and storage of study questionnaires for participants. In Finland, strong electronic identification enables participants to verify their identity safely in various electronic services before filling in PROMs.

The participants meeting inclusion and exclusion criteria will be invited by email to book the first research appointment from the internet time booking calendar. We anticipate needing 120 participants with CLBP to complete the clinical eligibility assessment and the study PROMs to recruit 30 participants. The sample size of 30 participants is a general recommendation for feasibility and pilot trials [51]. The sample size calculation for this feasibility study will not be calculated, because it is not recommended when there is no previous data from previous studies of similar study setting to inform this process [52].

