#### Randomization procedure

Thirty participants will be allocated by simple randomization prior to start of participant recruitment, with an allocation rate of 1:1. The random allocation list will be generated by the first author using the SPSS program. The participants will be included in the study in order of meeting the inclusion criteria and no exclusion criteria. They will subsequently book their first research appointment via the internet calendar booking system according to their timetables. Hence, the first author will be unable to decide in advance on the allocation group of the participant. Participants are blinded for intervention differences between groups.

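### Report a baseline-adjusted arm difference for each PROM, and do not judge responsiveness on within-arm change, which the entry cut-offs inflate for pain and disability

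*Protocol article*

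**What the plan says.** The Data analysis section calls the methods descriptive and gives a reporting format: "The results of the PROMs will be presented as means (Standard deviation or 95% confidence interval, lower and upper bounds". An outside analyst then compares the groups. The text names no contrast and does not say whether baseline scores enter it.

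Table 1 uses PROM results for progression in two ways: clinically relevant differences between the arms, and responsiveness as the basis for selecting the full trial's outcomes. The Objectives agree: changes in PROMs are to be quantified, among other things "to inform the choice of the most relevant and responsive PROM for a larger-scale study".

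Two of the ten PROMs also decide entry. The Eligibility criteria require "A numerical pain scale of 4 or higher on a scale of 0 to 10 to prevent floor effects in outcome measurement" and "Roland-Morris Disability Questionnaire score of 5 or higher on a scale of 0 to 24 to prevent floor effects in outcome measurement". Under Recruitment, candidates fill in the questionnaires at home after the clinic visit, and only those who qualify are invited to the first research appointment: "We anticipate needing 120 participants with CLBP to complete the clinical eligibility assessment and the study PROMs to recruit 30 participants". The Outcome measures section limits assessment to baseline and two months, to save resources. No second completion before treatment is described, so the screening scores are in effect the baseline.

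On size and allocation: "The sample size of 30 participants is a general recommendation for feasibility and pilot trials", and "Thirty participants will be allocated by simple randomization prior to start of participant recruitment, with an allocation rate of 1:1".

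**The concern.** There are two issues, with different causes and different remedies.

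1. **The contrast.** A progression decision is to rest on differences between arms, but the stated output is arm means. In arms of 15 formed by simple randomisation, a sizeable chance difference at baseline is likely on at least some of ten PROMs. Part of it would pass into any comparison of follow-up means. The baseline scores that would correct for this are already being collected.

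2. **The filter.** People admitted because a score was high on one occasion will on average score lower on the next, with or without treatment. This affects NPRS and RMDQ directly and the other eight scales only through their correlation with those two. If responsiveness is read from within-arm change, NPRS and RMDQ start ahead in the choice of the next trial's outcomes. The protocol justifies the cut-offs by floor effects and does not mention this side effect.

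**Working it through.** **The plan's own figures.** 15 + 15 = 30, and 30/120 = 25% screening yield. The sample size is a rule of thumb ("The sample size calculation for this feasibility study will not be calculated"), so it has no inputs to reproduce. The yield reflects all eligibility criteria and cannot tell how strongly the two score cut-offs select.

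**Inputs from the protocol.** n = 15 per arm; cut-offs NPRS ≥ 4 and RMDQ ≥ 5; NPRS MDC 1.5 and MCID 2; RMDQ MCID 2 to 3 (2.5 used here).

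**Assumptions (not in the protocol).** NPRS SD 2 with pre-screening mean 4–6; RMDQ SD 5 with pre-screening mean 5–9; baseline to two-month correlation r between 0.3 and 0.9; no treatment effect; no dropout.

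**1. Precision of the arm difference, unfiltered scale, in SD units**

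- Chance baseline difference: SE = √(2/15) = 0.365. The chance that it exceeds 0.5 SD in either direction on a given PROM is about 17%. A share r passes into the follow-up comparison; at r = 0.5, a one-SE imbalance shifts it by 0.5 × 0.365 = 0.18 SD.
- Follow-up means: half-width = t(28) × 0.365 = 2.048 × 0.365 = 0.748.
- Raw change: SE = √(2(1−r)) × 0.365.
- ANCOVA: SE = √(1−r²) × 0.365 × √(27/26), with t(27) = 2.052. At r = 0.5: 0.866 × 0.365 × 1.019 = 0.322, half-width 0.661.

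| r | Follow-up means | Raw change | ANCOVA | Narrower than follow-up | Narrower than change |
|---|---|---|---|---|---|
| 0.3 | 0.748 | 0.885 | 0.728 | 3% | 18% |
| 0.5 | 0.748 | 0.748 | 0.661 | 12% | 12% |
| 0.7 | 0.748 | 0.579 | 0.545 | 27% | 6% |

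On the filtered NPRS the gain is smaller, because truncation lowers the correlation (from 0.5 to about 0.38 at mean 5). In 20,000 simulated trials of 15 per arm (mean 5, SD 2), the SE for follow-up means against ANCOVA was 0.72 v 0.71 at r = 0.3, 0.69 v 0.65 at r = 0.5 and 0.65 v 0.53 at r = 0.7. The gains are about 1%, 6% and 18%.

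**2. Within-arm fall caused by the cut-off**

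Expected fall = (1−r) × SD × φ(z)/(1−Φ(z)), with z = (cut-off − 0.5 − mean)/SD.

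- NPRS, mean 5, r = 0.5: z = −0.75; 0.5 × 2 × 0.301/0.773 = 0.39 points.
- RMDQ, mean 7, r = 0.5: z = −0.5; 0.5 × 5 × 0.352/0.691 = 1.27 points.

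Simulation with whole-number, bounded scores gave these falls in points:

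| Scale, pre-screening mean | r = 0.5 | r = 0.7 | r = 0.9 |
|---|---|---|---|
| NPRS, 4 | 0.66 | 0.41 | 0.16 |
| NPRS, 5 | 0.40 | 0.25 | 0.10 |
| NPRS, 6 | 0.22 | 0.13 | 0.05 |
| RMDQ, 5 | 1.71 | 1.06 | 0.38 |
| RMDQ, 7 | 1.20 | 0.75 | 0.26 |
| RMDQ, 9 | 0.79 | 0.48 | 0.17 |

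That is 2–33% of the NPRS MCID and 7–68% of an RMDQ MCID of 2.5. The standardised response means are 0.05–0.35 and 0.07–0.39.

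With both cut-offs applied jointly (means 5 and 7, r = 0.5–0.7), the standardised response mean is 0.18–0.30 for NPRS and RMDQ. It is 0.09–0.18 for an unfiltered scale correlated 0.3–0.5 with them. A scale uncorrelated with both shows no fall.

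**3. Effect of the filter on the randomised contrast**

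The simulated mean arm difference was within 0.01 of zero with and without the filter. At r = 0.5 the SD of the difference in follow-up means was 0.69 with the filter and 0.73 without it.

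**The case against.** **Adjustment is not ruled out.** The Data analysis section gives a reporting format, and covariate adjustment is often left to a statistical analysis plan that is not shown here. This stands: a reader might infer that the plan commits to unadjusted comparisons, but the text does not say so. What remains is that the article names an output (arm means) that does not deliver the quantity Table 1 needs.

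**The filter does not harm the trial comparison.** A reader might infer that using the screening score as baseline biases the arm difference or makes it noisier. It does neither: both arms fall alike, and the filter slightly reduces the spread. Nor does ANCOVA remove the within-arm fall.

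**The size may be trivial.** This stands. If the 1.5-point MDC is a 95% limit and measurement error is the only source of variation, the standard error of measurement is 1.5/(1.96√2) = 0.54. Then r is about 0.93 at SD 2, and the NPRS fall is about 0.1 point or less. Even 0.66 is below the MDC. For comparison, the standard error of a standardised response mean in 30 people is roughly 1/√30 = 0.18, larger than the head start of the filtered scales over correlated unfiltered ones.

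**No responsiveness index is defined.** This also stands. The protocol speaks of the most relevant and responsive PROM and does not commit to ranking by pre-post change. It does say that changes will be quantified to inform the choice, so that reading is open and should be closed.

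**Two assessments were chosen deliberately.** The resource argument weighs against requiring a third, so the repeat baseline is offered only as an option.

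**Conclusion.** Both points hold in limited form.

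1. A baseline-adjusted difference is a free improvement on the output stated. Its gain over follow-up means is modest at low correlation and substantial at high correlation: 3%, 12% or 27% of CI width at r = 0.3, 0.5 or 0.7 on unfiltered scales, and about 1%, 6% or 18% of the SE on the filtered NPRS. A flat 25% variance saving should not be claimed, since it applies only to unfiltered scales at r = 0.5.

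2. Within-arm change on NPRS and RMDQ is inflated relative to the eight scales without a floor. The direction is certain whenever r is below 1. The amount, about 0.05–0.66 NPRS points and 0.17–1.7 RMDQ points, rests wholly on assumed means, SDs and r = 0.5–0.9. Other scales correlated with pain and disability share part of it.

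Two further inferences are not supported. The two scales need not come out as most responsive, because the head start may be small beside sampling error. Planning values for the full trial need not be too large either: a parallel-group trial is planned on the arm difference and its SD, and the same cut-offs, if reused, would produce the same fall again.

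**What to change.** - In Data analysis, state that for each PROM the baseline-adjusted mean difference between arms (ANCOVA) is reported with its 95% CI, beside arm means and SDs at both time points, as estimation without hypothesis testing. This costs nothing, as the data are already collected.
- In Objectives and Table 1, state that responsiveness for choosing the next trial's outcomes is judged on that contrast and not on within-arm change. This is also free. With half-widths of about 0.55–0.73 SD at r = 0.7 to 0.3, any ordering of ten PROMs will be imprecise, so the intervals should be shown with it.
- Where within-arm NPRS and RMDQ change is reported, state that the entry cut-offs inflate it.
- Optionally, repeat NPRS and RMDQ on the existing platform before the first session and use that completion as the analysis baseline, keeping the screening scores for entry only. This costs each participant a few minutes and adds one assessment to the planned two.

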## Discussion

SBTs are a simple, free and safe addition to exercises to potentially give them an improved multidimensional clinical outcome. A clear and easily clinically implemented SBTs protocol is presented in this study. To date, possible clinical outcome differences with an SBTs add-on to exercises have not been studied for otherwise identical clinical settings and exercises.

The positive feasibility outcomes of this study could raise questions about the generalizability of the SBTs add-on to other exercise interventions to improve clinical outcomes. Due to the multifactorial nature of CLBP, SBTs add-on could be one more functional piece in a biopsychosocial and individualised treatment puzzle where exercise is one of the basic pieces.

The next step after a possibly favourable outcome from this feasibility study would be an evaluation of the clinical outcome of the breathing add-on in a larger randomized controlled trial study that would include the most relevant and responsive PROM(s) as primary and secondary outcome measures, clinicians with different backgrounds and experience levels, multicentre clinical settings and other guideline-recommended adjunct therapies, such as pain neuroscience education.

### Strengths and limitations

The major strength of this study is the pragmatic and easy-to-implement SBTs protocol with well-documented and practically identical exercises to inform possible outcomes related to exercise with and without SBTs. The other main strengths of the study are the thorough and clinically relevant inclusion and exclusion criteria, with blinding of data analysts in relation to group differences and the study aims, in order to increase the reliability of results. As well as strength and limitation is the single-clinician study design, which is aimed at minimizing the intervention and contextual factor differences but which also affects the objectivity of exercise delivery by a single author and the generalisability of the study results for other therapists with less experience with SBTs. A second major limitation is the lack of intervention blinding for the therapist and participants, which is not generally possible in similar exercise intervention study designs.

#### Ethical approval and trial registration

Ethical approval for the study was obtained from the Research Ethics Committee of the Northern Savo Hospital District with identification number 2131/2022 on 31st January 2022. Written informed consent will be obtained from all participants before the study. The study is conducted according to the Declaration of Helsinki. The study has been registered with ClinicalTrials.gov Identifier: NCT05268822 on 8th February 2022. CONSORT 2010 statement: Extension to randomised pilot and feasibility trials were adopted upon reporting this feasibility trial protocol (Fig. 1) [85]. The SPIRIT checklist has been implemented to improve the content and quality of this protocol [86] and the CERT template was used to improve exercise reporting [87].

## Data Availability

Not applicable (NA).
